## Abstract

**Background:**

Cardiovascular diseases(CVD), specifically ischaemic heart disease(IHD), are the main causes of death in industrialized countries. Statins are not usually prescribed in the most appropriate way. To ensure the correct prescription of these drugs, it is necessary to develop, disseminate and implement clinical practice guidelines(CPGs), and subsequently evaluate them.

The main objective of this study is to evaluate the effectiveness of the implementation of consensual Lipid-lowering drugs (LLD) prescription guidelines in hospital and primary care settings, to improve the control of Low-Density Lipoprotein Cholesterol (LDL-C) levels in patients with IHD in the Terres de l'Ebre region covered by the Catalonian Health Institute. Secondary objectives are to assess the improvement of the prescription profile of these LLDs, to assess cardiovascular morbimortality and the professional profile and participant centre characteristics that govern the control of LDL-C.

**Methods/Design:**

Design: Quasi-experimental uncontrolled before and after study. The intervention consists of the delivery of training strategies for guideline implementation (classroom clinical sessions and on-line courses) aimed at primary care and hospital physicians. The improvement in the control of LDL-C levels in the 3,402 patients with IHD in our territory is then assessed.

Scope: Primary care physicians from 11 basic health areas(BHAs) and two hospital services (internal medicine and cardiology).

Sample: 3,402 patients registered with IHD in the database of the Catalan Institute of Health(E-cap) before December 2008 and patients newly diagnosed during 2009-2010.

Variables: Percentage of patients achieving good control of LDL-C, measured in milligrams per decilitre. The aim of the intervention is to achieve levels of LDL-C < 100 mg/dl in patients with IHD. Secondary variables measure type and time of diagnosis of IHD, type and dose of prescribed cholesterol-lowering drugs, level of physician participation in training activities and their professional profile.

**Discussion:**

The development of prescription guidelines previously agreed by various medical specialists involved in treating IHD patients have usually improved drug prescription. The guideline presented in this study aims to improve the control of LDL-C by training physicians through presential and on-line courses on the dissemination of this guideline, and by providing feedback on their personal results a year after this training intervention.

## Background

CVD, specifically IHD, is the leading cause of death in Europe overall, and specifically in Spain. It is also responsible for high morbidity and high economic health care costs. Therefore, it is of particular concern in the health plans in industrialized countries [1]. At present, CVD prevention is based on the detection and treatment of modifiable risk factors, including dyslipidaemia [1-4].

For DL, lipid-lowering treatment aims not only to reduce levels of the different blood lipids, but also to reduce the CV morbidity and mortality associated with them. It is considered that the value of LDL-C should determine the start of lipid-lowering therapy since there is strong evidence that such a reduction leads to a directly proportional reduction in CV risk [2,5]. Thus, hypercholesterolaemia is accompanied by a high prevalence of coronary disease in both sexes, explaining 19.4% of coronary events in men and 20.1% in women. The information currently available about the risk attributable to each of the cardiovascular risk factors (CVRFs) in the Spanish population is limited. Although we know the prevalence of these CVRFs we do not know very much about their control [6].

In order to improve the management of CVD and IHD various organizations have developed a number of CPGs and Expert Consensus Documents in recent years. These documents review the scientific evidence related to IHD, CVD CVRFs and CV prevention, critically assess the diagnostic and therapeutic procedures, and establish recommendations based on the profile of efficacy, safety, convenience and cost of a procedure or treatment, and assess the risk/benefit [1-3,5,7]. After developing these CPGs it is imperative to translate the knowledge they yield to professionals and thereby to clinical practice. Unfortunately, it is well known that professionals who should be using these CPGs are often unaware of them or simply do not implement them [8-10]. This is why it is necessary to develop strategies for CPG implementation that can overcome the difficulties and barriers in the setting in which they are going to be used. These strategies have had a favourable influence on clinical outcomes. It is also essential to make a final analysis of the results using polls and registers to verify whether physicians are implementing the recommendations of the guidelines in their clinical practice and to assess their impact on patients' clinical outcomes [8-10].

Some studies have aimed to determine the theoretical applicability of the GPCs by comparing results of clinical practice in the field of the DL and primary care. The RESPECT study [11] has shown moderate levels of agreement between theoretical calculations and routine clinical practice. Several clinical trials, in which the intervention consisted of the dissemination of guidelines for hypertension and DL, have reported an increase in the prescription of drugs, but no improvement in the quality of the management of hypertension and DL patients [11,12]. Another study of CPG implementation in primary care and CVD has shown the quality of care to be suboptimal. In this study, only 15-40% of patients achieved the treatment goals. Medical education interventions and subsequent audits offer improvements but there remains a gap between the recommendations and the reality [13].

In the health region of Terres de l'Ebre, there is particular interest in and concern to improve the management of patients with CVD. The Preseap study has recently been carried out in our area [14]. This aimed to improve the management of patients in secondary prevention of CVD, through a programme of intensive control based on medical visits by patients in their health centre. The results showed no differences between this group of patients and a control group who made regular visits [14,15]. In addition, the factors determining the control of LDL-C levels have been studied in patients with CVD. It was found that control of these factors differed within and between the various studies, an outcome that should be borne in mind when applying the current recommendations for achieving therapeutic goals in secondary prevention [16].

For this reason, a collaborative action between primary and hospital care units was instigated in 2008 to coordinate, harmonise and improve the management of patients with CVD in our area. Amongst these actions, a multidisciplinary CPG for the treatment of DL in secondary prevention of CVD has been planned, with technical advice from the Catalan Institute Pharmacology Foundation (FICF).

In this CPG, very general recommendations are made about the control of various CVRFs, and the non-pharmacological (lifestyle changes) and pharmacological DL treatments (especially hypercholesterolaemia) are also described in detail. In addition, the efficacy, safety, convenience, cost and risk-benefit ratio of various therapeutic interventions and their role in secondary prevention are evaluated. It also provides several tables for guidance to facilitate drug prescription by physicians based on the goals of LDL-C control for secondary prevention. Finally, an algorithm is proposed to improve patient control and follow-up.

In recent years, the need to promote research into primary care has become increasingly recognised, as exemplified by the many studies addressing the development of strategies to improve prescription quality and implementation of GPCs [10]. One of the great challenges that faces us at present is to ensure that all the professional involved adhere closely to the GPCs [7,17-20].

## Objectives

The main objective is to evaluate the implementation effectiveness of a set of lipid-lowering treatment guidelines in the primary care and hospital settings, and thereby to improve LDL-C lipid control in patients with IHD throughout the Terres de l'Ebre Region served by the Catalonian Institute of Health.

### Secondary objectives

- To evaluate the implementation effectiveness of the guidelines for improving the profile (type and dose) of LLD prescribed by physicians to patients with IHD.

- To assess CV morbidity and mortality.

- To determine how professional profile influences the impact and effectiveness of the intervention.

## Methods/Design

### Study design

The design is a quasi-experimental uncontrolled before-and-after study, investigating patients seen by physicians in primary care centres and hospitals in the Terres de l'Ebre region covered by the Catalan Institute of Health.

### Setting

All the Primary Care Areas (PCAs) of the Terres de l'Ebre provincial Health Region of Tarragona, Catalonia, Spain, have agreed to participate in this study. This will include physicians from the eleven PCAs and cardiologists and internal medicine physicians from the Hospital de Tortosa Verge de la Cinta.

### Study period

The study will be undertaken between January 2009 and January 2012.

### Study sample

The sample will include those patients registered in the database (e-cap programme) with different IHD-related diagnoses: myocardial infarction, stable angina or unstable coronary syndrome, and chronic myocardial ischaemia. In all, 3,402 patients (registered up to December 2008) will participate in this study, along with those newly diagnosed with IHD who have been registered in the e-cap programme during 2009 and 2010. All patients who do not meet the criteria of the attended population (i.e., those not making a minimum of three primary care visits over the previous two years, and at least one visit in the last year) will be excluded from the study. Patients with a terminal or serious illness will also be excluded.

### Intervention

The intervention has been designed to use different strategies for implementing the CPG in an attempt to increase the efficiency of lipid-lowering prescription for better control of DL in the patients in our health region. The intervention will be carried out by medical professionals through double training sessions with a brief refresher session of the GPC and provision of feedback of their personal results a year after the initial intervention.

The intervention targeted at the physician has two components

#### a) Presential training sessions and interactive workshops

Doctors from the 11 primary care centres and the two hospital services (Cardiology and Internal Medicine) will be informed about the CPG and the various measures of secondary coronary heart disease prevention (how to achieve the target levels of LDL-C). Two doctors (one from primary care and the other from a hospital), previously trained by the research team, will lead the sessions that will take place in each primary care centre and hospital service. Two types of session will be held:

- An initial two-hour training session.

- A one-hour refresher session, a year after the initial training session, where the initial results will be presented and attendees will be reminded of the key points.

#### b) On-line training course

On a voluntary basis, physicians involved in the study may take a 20-hour on-line course. Teachers will be physicians from the FICF.

### Measurements

First, a database will be set up to contain the cases diagnosed with IHD, wherein every case will be linked to the primary care physician and health centre. This will allow us to correlate the patient's degree of disease control with their sociodemographic characteristics, doctor's profile and primary care centre characteristics. We will analyze the number of patients with LDL cholesterol control (patients with LDL cholesterol < 100 mg/dl), mean of controlled patients (with LDL cholesterol < 100 mg/dl) per physician, number of patients with IHD by physician, types of IHD and years of disease progression. Patients with and without lipid-lowering therapy, treatment type, dosage and proper treatment of IHD (numbers of patients with: anti-aggregation vs. anticoagulation, beta blockers and angiotensin-converting enzyme inhibitors (ACEI)) will also be analysed.

The number of laboratory tests per patient before and after the intervention will be taken into account to assess the degree of patient control.

The profile of the clinicians who receive the intervention will include variables such as their attendance on the classroom course, completion of the on-line course, their socio-demographic characteristics, employment status, specialist by residency training system or not, and assistance quality standards (scored from 0 - 1000 on the basis of the recommendations of an expert group. This number is determined by the level of detection and control of the most prevalent diseases), standard of drug prescription (scored from 0 - 130 according to the annual prescription standards set by an expert panel). Finally, characteristics of each primary care centre, such as population assignment, population served, number of patients per doctor, status as a teaching or non-teaching centre, location in a rural or urban area, and whether a referral hospital, will also be examined.

#### Main independent variable

Percentage of patients who achieve a good control of LDL-C, measured in milligrams/decilitre (mg/dl). The control goal for IHD patients is LDL-c < 100 mg/dl.

At the beginning of the study, a patient will be considered to be controlled if the most recent measured level of LDL-C (in 2008) is < 100 mg/dl.

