#### Number of laboratory tests of LDL-C

- Number of laboratory tests of LDL-C performed before (in 2009), during (2010-2011) and after the intervention (in 2012) in patients with an IHD diagnosis.

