### Forecast execution dates

The project will be carried out over three years.

September 2009: presentation of training material, standardized training for trainers.

January 2010: classroom and face-to-face satisfaction survey.

March 2010-June 2010: on-line course.

January 2011-March 2011: post-intervention analysis of results.

May 2011 Feed-back and reminder of GPC.

January 2012-September 2012: data processing, statistical analysis, data interpretation, preparation and dissemination of results.

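### The primary baseline is the last 2008 LDL-C, but classroom training starts in January 2010, so 12 to about 24 months of pre-training change, in either direction, cannot be separated from the training effect

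*Protocol article*

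**What the plan says.** Under "Main independent variable", the protocol article sets the baseline status: "a patient will be considered to be controlled if the most recent measured level of LDL-C (in 2008) is < 100 mg/dl".

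Under "Forecast execution dates", the activities run in this order:
- preparation: "September 2009: presentation of training material, standardized training for trainers"
- first sessions for physicians: "January 2010: classroom and face-to-face satisfaction survey"
- voluntary course: "March 2010-June 2010: on-line course"

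For another variable the before-year is different: "Number of laboratory tests of LDL-C performed before (in 2009), during (2010-2011) and after the intervention (in 2012").

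The Background section adds that "a collaborative action between primary and hospital care units was instigated in 2008" to improve the care of cardiovascular patients in the area. It lists the guideline under study as one of the actions planned within it.

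The analytical strategy compares LDL-C control at baseline and at the end of the study with a McNemar test. It then fits a logistic and a multilevel logistic model with an intervention term, adjusted for baseline values and confounders. No calendar-time or trend term is named. The Discussion acknowledges that there is no control group, but does not mention the interval between the 2008 baseline and the 2010 training.

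**The concern.** In an uncontrolled before-and-after study, whatever changes between the two measurements is read as the effect of the intervention. The usual protection is to measure the before value as close to the start of the intervention as possible. Here the before value is at least a year older than the first physician session. A change in LDL-C control during 2009 from any other cause would be added to the training effect if control rose, or subtracted from it if control fell. Other parts of the 2008 collaborative action are one possible cause.

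The protocol also uses two before-years: 2008 for LDL-C control and 2009 for the number of LDL-C tests. Results for the two variables would therefore describe different pre-intervention periods. The 2008 rule also does not fit patients first diagnosed in 2009 or 2010, who enter the sample but have no 2008 value as patients with ischaemic heart disease.

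**Working it through.** **1. The plan's own sample size.** Inputs from "Sample size": 35% controlled, an increase of 10%, 25 patients per physician, a value of 0.05 (labelled a confidence interval), two-sided alpha 0.05, 90% power, 20% loss.
- Two proportions, 35% against 45%: 503 per group. Design effect 1 + (25 − 1) × 0.05 = 2.2. Then 503 × 2 × 2.2 / 0.8 = 2,766.5, against the stated 2,761.
- With continuity correction and a loss factor of 1.2: 523 × 2 × 2.2 × 1.2 = 2,761.4.

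The figure reproduces, so the sample size is not at issue. The check shows that the expected gain is 10 percentage points and that 0.05 works as an intracluster correlation. Both are used below.

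**2. Length of the gap.**
- Shortest: 31 December 2008 to 1 January 2010, 12 months.
- Longest: 1 January 2008 to January 2010, 24 to 25 months.

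The date of the final LDL-C is not stated. If it is about January 2012, the end of the study period, the pre-training share of the compared interval runs from 12/36 (one third) to 24/48 (one half).

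**3. What a drift would do to the planned test.** The documents give no trend, so the drift d is assumed. Other inputs:
- Pairs: 3,402 × 0.8 = 2,722 (registered patients less the protocol's 20% loss).
- Baseline proportion p0 = 0.35; later proportion p1 = 0.35 + d.
- Within-patient correlation r = 0.2 to 0.4 (assumed).

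Formulas:
- p11 = p0·p1 + r·√[p0(1 − p0)·p1(1 − p1)]
- discordant share D = p0 + p1 − 2·p11
- standard errors SE0 = √(D/n) and SE1 = √[(D − d²)/n]
- probability of significance ≈ Φ[(d − 1.96·SE0)/SE1], plus a negligible opposite tail for all but the smallest drifts

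Example, d = 0.03 and r = 0.2: p11 = 0.1330 + 0.2 × 0.2315 = 0.1793. D = 0.73 − 0.3586 = 0.3714. SE0 = √(0.3714/2,722) = 0.01168. The probability is about 0.73.

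Probability of a significant result with no training effect at all:

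| Total drift (points) | Share of the planned 10 points | McNemar as planned | Variance × 2.2 |
|---|---|---|---|
| 1 | 10% | 14-17% | 9-10% |
| 2 | 20% | 40-51% | 21-27% |
| 3 | 30% | 73-84% | 41-52% |
| 5 | 50% | about 99% | 82-91% |

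The last column replaces n by 2,722/2.2. It stands in roughly for an analysis that allows for clustering by physician, as the multilevel model would. The nominal rate is 5%.

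**4. The analysis.** The McNemar test uses only the two statuses. The regression models adjust for baseline values and confounders, but the intervention term is itself the before/after contrast, so pre-training change stays inside it.

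**The case against.** Several points on the other side have force.

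- **The 2008 choice has a rationale.** The cohort is registered up to December 2008, the 35% planning figure is 2008 data, and "The study will be undertaken between January 2009 and January 2012". A 2008 value is the natural one for the start of the study period. That stands as an explanation. But closing the cohort in December 2008 does not require the baseline LDL-C to come from 2008, and the training starts a year after the study period opens.
- **The lack of a control group is disclosed.** It is, and a later baseline would not make the study controlled: change from 2009 onwards would still be counted as training effect. The point here is only the additional, avoidable gap.
- **The test-count window is a weak authority.** It places the after-period in 2012, although the study period ends in January 2012 and a post-intervention analysis is scheduled for early 2011. This is fair, and it is a reason to reconcile the windows, not to keep two of them.
- **Some activity precedes January 2010.** Trainers are prepared in September 2009, and training material is presented then to an audience that is not stated. A reader might infer that nothing at all reaches physicians before 2010. The documents do not support that, because the trainers are themselves a primary care doctor and a hospital doctor. A 2009 baseline would overlap slightly with this preparation.
- **The 2008 action is not a clean rival cause.** A reader might infer that a separate programme was already raising control in 2009. The guideline is itself one of that action's components, and the documents name no other component delivered to patients in 2009. They support only that other parts could contribute.

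**Conclusion.** The point holds on the protocol's own dates. Baseline control is fixed in 2008, physicians are first trained in classroom sessions in January 2010, and 12 to about 24 months of change enter the primary contrast with no stated analysis to separate them. Two before-years also appear for related LDL-C variables.

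The size of any bias cannot be derived from the documents. The table rests on an assumed drift, an assumed correlation of 0.2-0.4, 2,722 pairs and, in its last column, a variance inflation of 2.2. It shows that a drift of 2 or 3 points, well below the planned 10, could produce a significant result fairly often, while a drift of 1 point would do so much less often. It does not show that such a drift will occur.

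A reader might infer that the bias is most likely upward. Nothing in the documents supports that. No trend in LDL-C control is given, and the one local programme of intensified control described in the Background showed no difference from usual visits. A fall during 2009 would hide a real effect just as a rise would mimic one.

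**What to change.** Reconcile the baseline definition, the test-count windows and the calendar of activities, as follows.

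1. Define the primary baseline as the last LDL-C in the 12 months before the January 2010 sessions, for the cohort registered by December 2008.
2. Analyse patients newly diagnosed in 2009-2010 separately. Their 2009 value may precede treatment, and including it in the primary pairs would bring a bias of its own.
3. Keep the 2008 value as a second pre-measurement, and report the 2008-to-2009 change beside the change from 2009 to the end of the study. This is one pre-training interval, so it is a limited check on background drift.
4. Report how many patients lack a 2009 test, and repeat the main analysis with the 2008 baseline as a sensitivity analysis.

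The cost is a changed date in one definition and one further extraction from the e-cap database. The required sample size does not change. Patients with no LDL-C test in 2009 leave the primary pairs, in a number the documents do not allow one to estimate. Individual baseline values may still be up to a year old, and drift after 2009 remains uncontrolled.

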#### Secondary variables

##### IHD

- Type: Acute myocardial infarction, stable and unstable angina, acute coronary syndrome and chronic myocardial ischaemia.

- Time since disease diagnosis (diagnosis date)

